#### Secondary analysis

To address the first secondary question, to what extent physiological sensor data can serve as proxies for concentration changes, as measured by the cognitive task, we will use descriptive and visual analytics. Time-series plots, condition-wise summaries, and participant-level comparisons will be generated to explore signal patterns across the intervention and control phases. If sensor data is missing, we will not impute the data and report only cases where we observe the sensor data for at least 60 consecutive seconds in every period. Summary statistics such as means, standard deviations, medians, and interquartile ranges will be computed for each physiological signal, stratified by condition (music vs. no music) and participant. Visualizations may include line plots, box plots, and heat maps to explore temporal dynamics and individual differences. Furthermore, methods from time series analysis will be applied to detect changes before and after incorrect answers, thereby elaborating on the stress and concentration levels in relation to the given answer within this time frame.

To explore the second secondary research question, the extent to which individual differences such as music preference or playing an instrument moderate the effect of music on cognitive task performance, we will first stratify the descriptive statistics described in Section 2.5 for different subgroups. Subgroup analyses will be conducted only for groups that include at least five participants meeting the specific criteria. First, we will investigate listening behavior and music preferences. For this analysis, we will distinguish between participants who often or always listen to music at work and those who listen only occasionally, rarely, or never. Next, we will investigate the subgroup of participants who have ever played an instrument (Answers *Yes* and *Not anymore*). Finally, we will include these variables of interest with uninformative priors (β∼N(0,1)) as interaction effects in the Bayesian generalized linear mixed model (GLMM) used for the primary research question. We will adjust the model for the individual characteristics and experience and report the estimated effect and its estimated 95% credible interval for each model.

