### Objectives

1.1

This study investigates the effect of music on concentration through a rigorous experimental design, assessing individual changes in attention levels. By including various music genres chosen by the study participants, this study will contribute to understanding the role of music in cognitive performance, ultimately providing insights into whether and potentially how music can enhance concentration.

The study addresses one primary and two secondary research questions.

•*Primary research question:* Does listening to music from a self-selected genre influence cognitive task performance compared with a no-music condition, on average on the population level and for how many individual participants?

Secondary research questions:

1.To what extent can physiological sensor data (e.g., Electroencephalography (EEG), Heart Rate Variability (HRV), Electrodermal Activity (EDA), Eye Tracking) serve as proxies for concentration changes, as measured by the cognitive task?2.To what extent do between-person differences in intervention effects on cognitive task performance be explained by effect modifiers (e.g., music preference, baseline characteristics, physiological traits)?

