#### Outcomes

The primary outcome in our study is concentration, which will be assessed through the number of correct responses from the participant on a concentration task. For that, we will use an adapted version of the Stroop test tailored for a digital environment. The Stroop test is a well-established neuropsychological assessment designed to evaluate the ability to inhibit cognitive interference and maintain selective attention [33], [34]. In our adapted Stroop test, study participants will view words displayed in different colors (see Fig. 2). When the ink color matches the word’s meaning, participants are instructed to press the key *’r’*, and the key *’w’* if they do not. The system will further record the reaction time (i.e., the time between when the word is shown until a key is pressed). This modification ensures the test is compatible with the digital setup while maintaining its ability to measure concentration and cognitive control.

For answering the secondary research questions, sensor data defined below will be used.Fig. 2Screenshots of the adapted Stroop test. The top-left corner shows the phase’s remaining time, and a gray progress bar below the word indicates the time left for the current word.Fig. 2

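### The stated analysis for secondary question 1 gives no estimate of how far sensor signals follow Stroop performance; its only link to responses is an error-locked look with no stated comparator or association measure

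*Protocol article*

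**What the plan says.** The Objectives section asks to what degree sensor data can "serve as proxies for concentration changes, as measured by the cognitive task". The Outcomes section ties these data to the secondary questions: "For answering the secondary research questions, sensor data defined below will be used".

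The Secondary analysis section then states the approach for this question: "we will use descriptive and visual analytics". It has two parts.

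- **Summaries and plots.** Time-series plots, summaries by condition and participant-level comparisons are made "to explore signal patterns across the intervention and control phases". Means, standard deviations, medians and interquartile ranges "will be computed for each physiological signal, stratified by condition (music vs. no music) and participant".
- **A look around errors.** The paragraph closes by saying that "methods from time series analysis will be applied to detect changes before and after incorrect answers", with the aim of "elaborating on the stress and concentration levels in relation to the given answer within this time frame".

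Sensors are voluntary (Sensor data section). Missing sensor data are not imputed, and a case is reported only if every period has at least 60 consecutive seconds of signal.

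**The concern.** A proxy question is about the relation between two variables: when Stroop performance changes, does the signal change with it, and by how much? The summaries by condition involve only one of the two. A signal may differ clearly between music and silence and be unrelated to accuracy. It may also follow accuracy within both conditions and show no difference between them. The Introduction already reports that music alters EEG patterns and influences HRV and EDA, so a condition difference is to be expected for reasons unrelated to performance.

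The error-locked look does involve Stroop responses, but its stated output is the detection of changes, not their size relative to anything. At stake is one of only two secondary questions, and the one that most directly motivates collecting the sensor streams. The report could hold many condition-stratified sensor tables under a proxy question and still give no figure for proxy validity.

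**Working it through.** The protocol states no figure for this analysis, so there is none to reproduce. The check sets question against method, then asks what the data could support.

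**1. Question against method.**

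| Stated item | Uses Stroop responses? | Gives a degree of association? |
|---|---|---|
| Time-series plots, condition-wise summaries, participant comparisons | Not stated | No |
| Mean, SD, median, IQR by condition and participant | No | No |
| Time-series methods around incorrect answers | Yes | None stated |

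The third row is a real link. It lacks a stated comparator, and one is needed: at the assumed 1.2 s per answer (Sample size section), a window of a few seconds before or after an error also covers neighbouring responses, most of them correct. A change around errors can be read only against the same windows around correct answers.

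**2. Are there errors to analyse?** Inputs from the Sample size section: 150 responses per period, two periods per condition, 95% correct without music and 96% with music.

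- Without music: 2 × 150 × 0.05 = 15 errors.
- With music: 2 × 150 × 0.04 = 12 errors.
- Total: 27 per participant, and 23 × 27 = 621 if all 23 wear sensors. This is an upper figure, because sensors are voluntary.

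The error-locked part therefore has material to work on.

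**3. Precision of a period-level within-person correlation.** With n participants and 4 periods, df = n(4 − 1) − 1. The 95% half-width at r = 0 is tanh(1.96/√(df − 2)).

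- n = 23: df = 68; tanh(1.96/√66) = tanh(0.241) = 0.237.
- n = 15 (an assumed number with usable sensors): df = 44; tanh(1.96/√42) = tanh(0.302) = 0.294.

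**4. How large could that correlation be?** Take the true probability of a correct answer as a perfect proxy, under the protocol's power model.

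- Binomial SD of one period's accuracy: √(0.95 × 0.05/150) = 1.78 percentage points without music and √(0.96 × 0.04/150) = 1.60 with music. The assumed condition difference is 1 point.
- True within-person sum of squares: 4 × 0.005² = 0.000100.
- Expected noise sum of squares: 3 × (0.95 × 0.05 + 0.96 × 0.04)/300 = 0.000859.
- Approximate correlation: √(0.000100/0.000959) = 0.32.

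Simulating the same model with random-intercept variance 0.05 gives a mean of 0.33 with 23 participants and 0.33 with 15. The half-widths in step 3 are therefore most of the distance from zero to what a perfect proxy would show.

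**5. Effect of adjusting for condition.** In the power model, condition is the only source of within-person change in true accuracy. Adjusting for it leaves nothing for a sensor to follow; leaving it out lets the direct effect of music on the signal enter. Neither version is enough alone.

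**The case against.** The strongest reply is that the plan does relate sensors to Stroop correctness. A reader who stops at the condition summaries might infer that it never does, or that the stated method could not produce the quantity asked for. The text does not support either reading. The error-locked sentence links the signals to correctness, and because errors occur inside a period, where condition is constant, that comparison is free of the between-condition effect of music. Time-series methods could include a numerical association; nothing stated rules it out.

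It can also be said that windows, features and comparators are details an article may leave to a fuller plan, that the aim is exploratory, and that a period-level model has little power. The exploratory aim and the limited precision stand. The argument from condensed detail stands for windows and feature definitions, but not for the choice of method. The next paragraph of the same section takes secondary question 2, also framed as a matter of extent, and gives it interaction terms in the Bayesian mixed model with priors and 95% credible intervals. For question 1 the article names a descriptive approach instead. That is a stated choice that does not match the question.

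**Conclusion.** The point holds in a limited form. The analysis stated for secondary question 1 is descriptive and organised by music condition. Its one link to Stroop responses has no stated comparison with correct answers and no stated association measure, so as written it delivers no estimate of extent. Signal differences between conditions should not be read as proxy evidence, since music may act on arousal directly.

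It would be wrong to go further and claim that a period-level correlation would settle the matter. With a ceiling near 0.33 under the power model and half-widths of about 0.24 (23 participants) or 0.29 (15, assumed), such an estimate would be imprecise. The ceiling rests on 150 responses per period, rates of 95% and 96%, and no true within-person variation beyond condition; real variation between periods would raise it. The primary analysis is not affected.

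**What to change.** For one named feature per signal, add an exploratory within-participant association model built on the primary logistic mixed model:

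- **Outcome:** correctness of each response, or accuracy in short windows; accuracy per period for slow features such as HRV.
- **Predictors:** the person-mean-centred sensor feature and time, with a participant random intercept. Windows around errors are then compared with windows around correct answers.
- **Report:** the odds ratio with a 95% credible interval, both with and without adjustment for condition.
- **Keep** the planned plots and summaries as support, and state that precision is limited and that period-level correlations are attenuated by binomial noise.

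If no such model is added, reword question 1 as a description of sensor patterns by condition and around errors.

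The cost is a short wording change and one extra exploratory model per signal. No new data are needed.

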#### Interim analysis

Immediately after the end of each trial, individual descriptive statistics will be calculated and reported to the participant, who can discuss them with the study conductor. This report presents the absolute and relative numbers of correctly classified answers, represented in a contingency table, as well as the average time spent answering the task in each period. Neither the sensor data nor the questionnaire data will be analyzed in the interim analysis. For the individual-level analyses, credible intervals will be computed. No p-values nor confidence intervals will be calculated on an individual level at this stage. The study participants will be informed that they should not communicate the results to others until the study is completed, to avoid interference, i.e., influencing trials of other participants.

### Data handling

2.6

#### Collection and management

Before participating in the study, each participant will receive detailed information about data collection, storage, and deletion protocols. Participants will also be informed that study data will be published anonymously, linked only to a randomly generated pseudonym.

Study data will be collected on-site using Python and stored anonymously on local devices at the institution, with no retention of names, email addresses, or other personal data. A random pseudonym will be generated and provided to each participant, allowing only the participant to re-identify their own data. This is part of an irreversible anonymization process to ensure data security and privacy.

The data can only be deleted at the in-person meeting, as after the in-person meeting, the data cannot be retracted.

The data will be analyzed by trained investigators from the institute and the university. After the study is finished, anonymized data as well as the code base for conducting the experiment will be published online under the CC BY-NC license. The code will be published through GitHub, and the data through a suitable data sharing platform, along with the data description. The data sharing statement can be found in Table 3.

**Table 3 tbl3:** Data sharing statement.

Element	Attribute
Will individual participant data be available?	Yes

What data in particular will be shared?	All of the anonymized individual participant data, including questionnaires and sensor data if possible, will be shared

What other documents will be available?	Study Protocol, Analytical Code

When will the data be available?	Immediately after the publication, without an end date.

With whom?	Anyone who wished to access the data

What type of analysis?	Any non-commercial purpose (CC BY-NC license)

By what mechanism will data be made available?	An online repository will be set up

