#### Recruitment

The study population will be recruited from the University of Potsdam and the surrounding community until reaching 23 participants. The study will be advertised on several channels: posters at the university, announcements on the institutional website, email distribution lists, and social media channels (LinkedIn, Instagram). The material will include the title of the study, a short introduction, a contact address, and a reference to the detailed project website. Interested individuals can contact the study team by email promoted in the material. Upon contact, potential participants will receive further information about the study and a short eligibility screening. Eligible individuals will be invited to schedule an on-site appointment. At the beginning of the session, the study purpose and procedures will be explained, and written informed consent will be obtained before participation. A thank you gift in the form of sweats will be offered after finishing the trial, but no course credits nor financial incentives will be given to the study participants.

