#### Study registration

Interested participants schedule an initial meeting through direct contact via email. Available time slots for onsite participation are shared, and an appointment will be scheduled.

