#### Discussing results and feedback session

Upon completing the trial, participants receive an overview of their preliminary results, including the preliminary results of the individual Bayesian analysis described in detail in Section 2.5. A brief feedback session allows participants to share their experiences, preferences, and impressions of the study.

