#### Estimand

In order to define the estimand of interest, we specify the population, intervention, endpoint, summary, and intercurrent events following the ICH-E9 (R1) statement for estimands. The population includes all enrolled participants who start the trial. The participants are exposed in the intervention condition to music from their self-selected music genre. In the control condition, no music will be played. The endpoint is the binary outcome of each Stroop trial (correct vs. incorrect), measured repeatedly within the periods. For each participant and condition, we will summarize performance as the proportion of correct responses. The estimand of interest is the population-level average effect of music on concentration, estimated as the average across participants of the within-participant differences in the Stroop proportions between music and no-music periods. Additionally, we are interested in individual-level intervention effects, estimated as within-participant differences in the primary outcome between music and no music conditions. Missed responses are counted as incorrect; besides that, no intercurrent events are expected.

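### Participants see their own music versus no-music result while they can still have their data deleted, so who is analysed can depend on the primary outcome

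*Protocol article*

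**What the plan says.** The study is one on-site appointment. Under Study registration: "Available time slots for onsite participation are shared, and an appointment will be scheduled". Consent is taken at the start of that session, the four periods follow, and results and feedback come last (Section 2.4).

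- **Result shown to the participant.** The feedback step in Section 2.4 reads: "Upon completing the trial, participants receive an overview of their preliminary results, including the preliminary results of the individual Bayesian analysis". Interim analysis (Section 2.5): "Immediately after the end of each trial, individual descriptive statistics will be calculated and reported to the participant". On the content of that report: "This report presents the absolute and relative numbers of correctly classified answers, represented in a contingency table". The number of correct answers is the primary outcome, and the individual analysis contrasts music with no music.
- **Deletion.** Collection and management (Section 2.6): "The data can only be deleted at the in-person meeting, as after the in-person meeting, the data cannot be retracted". No point within the meeting is named as the last one for this choice.
- **Population.** Estimand (Section 2.5): "The population includes all enrolled participants who start the trial".
- **Target.** Recruitment (Section 2.1): "The study population will be recruited from the University of Potsdam and the surrounding community until reaching 23 participants". The text does not say whether someone whose data were deleted counts towards 23 or is replaced.

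**The concern.** Read in order, these sections let a participant decide whether to keep their record with their own primary-outcome contrast in view. Each participant has picked the genre they expect to help their concentration most, so a result that contradicts this choice could be a reason to discard it. If retention follows the observed difference between conditions, two things are distorted: the population-level effect, and the number of individuals who appear to benefit. Both belong to the primary research question. The planned effect is only 1 percentage point and the trial has only 23 participants, so a few such deletions could matter. The deleted values could not be recovered. Missing single responses have a rule (counted as incorrect), but a missing participant has none.

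**Working it through.** **1. Order of events.** Consent, four periods, result and feedback, end of meeting. Deletion is possible until the meeting ends and the result is shown before that. No sentence places the deletion choice earlier. The article does not define exactly when the meeting ends, but a result reported immediately after the trial and discussed with the study conductor falls within it on any natural reading.

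**2. Inputs (Sample size, Section 2.1).** 95% correct without music, 96% with music; 150 responses per period, hence 300 per condition per participant; 23 participants; Wald z-test at 0.05, taken as two-sided; random-intercept variance 0.05.

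**3. The plan's own power.** With 300 × 23 = 6,900 responses per condition:

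- SE = √[(0.95·0.05 + 0.96·0.04)/6,900] = √(0.0859/6,900) = 0.00353
- z = 0.01/0.00353 = 2.83
- power = Φ(2.83 − 1.96) ≈ 80.9%

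Simulating from Eq. (1), with a participant-stratified Mantel-Haenszel log odds ratio and Wald test in place of the mixed model, gives 81.6%. The plan states 81.3%. It reproduces, so the sample size is not at issue.

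**4. Spread of one participant's difference.** SD = √(0.95·0.05/300 + 0.96·0.04/300) = 1.69 points. SE of the mean over 23 = 1.69/√23 = 0.353 points.

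**5. Worst case.** Assumption: no true effect, and exactly the k records least favourable to music are deleted. Differences are drawn as normal with SD 1.69, the lowest k are dropped, and the mean of the rest is tested at its nominal SE. Ranges cover 23 starters without replacement and refilling to 23.

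| k deleted | Shift in mean (points) | Two-sided error |
|---|---|---|
| 1 | about +0.15 | about 6.5% |
| 2 | +0.26 to +0.28 | about 10.7% |
| 3 | +0.36 to +0.39 | about 16% |

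For k = 2 and 3 nearly all the false positives favour music. A binomial simulation with 95% correct in both conditions, intercept variance 0.05 and no replacement agrees: +0.16, +0.29 and +0.41 points, with errors of 6.6%, 10.3% and 16.4%.

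**6. Milder assumption.** Suppose a share q of participants with an observed difference below zero delete, again with no true effect and no replacement.

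| q | Bias (points) | Two-sided error | Mean number kept |
|---|---|---|---|
| 10% | +0.08 | 5.1% | 21.9 |
| 20% | +0.16 | 6.8% | 20.9 |
| 30% | +0.24 | 8.9% | 19.8 |
| 50% | +0.46 | 17.1% | 17.7 |

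Refilling to 23 does not remove the problem: the error is 9.2% at q = 30% and 22.7% at q = 50%.

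**7. Deletion on overall score.** Deleting the two lowest total scores under no true effect gives a bias of 0.00 points and an error of about 5%. The effect is a within-person contrast, so only deletion that follows the contrast biases it.

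**The case against.** Several stronger readings are tempting, and the documents do not support them.

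- **Deleted records leave no trace.** Identities are not linked to study IDs, so a reader might infer this. But signed consent forms are kept (Consent to study; Confidentiality), end-of-session reports are stored (Monitoring), and deviations are documented (Auditing). The number of deletions could largely be reconstructed. What is lost is the values, and no step described records whether deletion came before or after feedback.
- **Deleted participants are replaced.** Recruitment does not say so. The size of the bias hardly depends on it.
- **The estimand is contradicted.** The Estimand section defines a target population, and a right to erase data creates missing data without redefining that target. Deletion after all four periods is also not an intercurrent event, because the outcome has already been measured. What stands is that the analysed set may differ from that population.
- **Anyone who scored badly would bias the result.** Step 7 shows otherwise.
- **The bias must favour music.** The choice of genre makes this plausible, but deletion of results favourable to music would push the other way.

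There are three further fair points. Nothing hangs on the score for participants, so few may delete. The primary analysis is Bayesian and has no 5% decision rule; the error rates above belong to the test used for the power calculation, although the planned prior on the effect would not remove a selection bias. Finally, the full protocol or consent form may fix the timing. The article, however, does state both the deletion window and the feedback step, and as stated they overlap.

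**Conclusion.** The point holds as a gap in the order of steps at the visit. As written, deletion stays open after the primary result is shown, so retention can depend on it. The documents do not show that deletions will occur, how many, or in which direction. With none, the bias is zero; if 10% of those with an unfavourable difference delete, it is negligible. In the worst case of two deletions, the spurious shift is about a quarter of the planned effect and the nominal 5% error roughly doubles to about 10.7%. These figures rest on the planning rates, 300 responses per condition, no true effect, and deletion driven purely by the observed contrast. The reason to act is that lost values cannot be restored afterwards, while prevention is cheap. This is a change worth making before recruitment, not a flaw that invalidates the design.

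**What to change.** In Discussing results and feedback session and in Collection and management, state that each participant confirms keep or delete after period 4 and before any result is displayed, and that this is the last point for deletion. Put the same sentence in the consent form.

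If deletion must remain possible after feedback, keep an anonymous count of deletions before and after the result display, and report it together with the number who started.

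Cost: one extra screen in the Python script, one sentence in the consent form, and an ethics amendment under the protocol's own amendment rule. The downside is a slightly earlier cut-off for deletion. Participants keep both their right to delete and their feedback, and no extra participants are needed.
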